**Precis**

Uric acid (UA) is a terminal product of purine metabolism with strong antioxidant properties. UA has sizeable concentrations in biologic fluids only in humans and primates because they have a non-functional mutation of the enzyme uricase that, in other animals, transforms UA to allantoin. It has been hypothesized that this mutation has emerged evolutionarily because through this mechanism, humans can counteract the excessive oxidative stress that occurs in many critical pathologic conditions. Partially in contrast with this theory, high levels of UA have been associated with a number of negative health outcomes, including cardiovascular as well as all-cause mortality. Although it is possible that the UA elevation is merely a marker of critical health because it is an “inducible” antioxidant, researchers have questioned whether UA has beneficial or detrimental effect on health status. For example, we recently demonstrated that higher UA levels are cross-sectionally associated with higher levels of pro-inflammatory markers, and predict the increase in inflammatory markers over a 3-year follow-up. Understanding whether UA exerts a protective or detrimental effect on health is important in deciding whether mild hyperuricemia should or should not be aggressively treated.

Unfortunately, observational studies cannot fully address this question. In fact, we cannot exclude that the cross-sectional and longitudinal association between UA, inflammatory markers and negative health outcomes, may simply reflect the fact that UA is an inducible antioxidant that is produced in response to increasing oxidative stress. To verify the hypothesis that UA activates inflammation, we plan to conduct two complementary randomized controlled trials, each one including 10 treated and 10 control subjects. In the first trials, subjects with low UA will be administered 500 mg of UA intravenously. In the second trials, subjects with moderately elevated UA will be administered a single acute dose of Rasburicase. Then inflammatory markers will be measured at multiple points in time, for a total of 32 hours. We hypothesize that an acute increase in the circulating levels of UA will be followed by increasing levels of inflammatory markers. At the same time, an acute reduction of UA levels will be followed by a progressive reduction of inflammatory markers. This study should provide information that will help clinicians to decide whether to or not to treat mild hyperuricemia.

**1. Background and RationalE**

The relationship between UA (UA), inflammation, and chronic diseases is attracting attention in the scientific community. Epidemiological studies suggest that hyperuricemia is an independent risk factor for diabetes, impaired fasting glucose (1), insulin resistance (2), and hypertension in the general population (3-5). High UA concentrations have been associated with both recurrence of stroke (6) and high risk of cardiovascular events in subjects affected by hypertension or pre-existing cardiovascular disease (7). Moreover, UA is a strong negative prognostic factor in patients affected by chronic heart failure (8), and an independent predictor of cardiovascular (9), and all-causes mortality (10).

Since inflammation and oxidative processes are involved in the pathogenesis of all these conditions (11-15) and UA is chemically a strong antioxidant it has been suggested that UA may limit the damage caused by the increased oxidative stress. The antioxidant and, more in general, the biological effect of UA in humans “in vivo” has been little studied. In a series of healthy volunteers, intravenous systemic administration of 1000 mg UA was associated with higher increase of the serum total antioxidant capacity compared to placebo (16,17). In subjects who performed a bout of acute exercise for 20 min, pretreatment with intravenous solution of UA blunted the increase of circulating 8-isoprostaglandin F2α (an oxidation product) that occurs during strenuous exercise compared to controls (18). Recently, a solution with 500 mg of UA has been administered to a group of regular smokers, type 1 diabetics and adult controls who reported an improvement in the endothelial function. The infusion of 500 mg and 1,000 mg UA was well tolerated, with no side effects or change in clinical, hemodynamic and biochemical parameters (16-19).

However, a number of pre-clinical and clinical studies suggest that UA may be a pro-inflammatoryfactor *per se* (20) and the potential beneficial effects of its antioxidant activities can be partially or completely overcome by its proinflammatory properties.

Preliminary data from our group showed that in a representative sample of community-dwelling elderly participants, abnormally high UA levels as well as UA concentrations in the upper portion of the physiologic range are associated with high levels of several inflammatory markers, such us White Blood Count (WBC), neutrophils, C-reactive protein (CRP), interleukin-6 (IL-6), interleukin-18 (IL-18), interleukin-1 receptor antagonist (IL-1ra), and tumor necrosis factor-alpha (TNF-a) (21). Furthermore, baseline UA concentrations and UA changes significantly predicted IL-6 and CRP levels after three years (22). These findings are consistent with the association between serum UA and CRP levels which has been described in previous epidemiological studies (23)

Circulating UA levels increase over the lifespan as observed in a large observational longitudinal population-based study (24). Since aging has been consistently associated with higher levels of circulating inflammatory markers (25), a possible pro-inflammatory activity of UA may contribute to the mild inflammatory state of the elderly. Exploring the possible causes of chronic inflammation in the older population is important because inflammation is one of the fundamental pathophysiological mechanisms underlying the major chronic diseases and the development of disability in the elderly.

Although the intra-articular pro-inflammatory activity of monosodium urate (MSU) crystals, the saline form of UA involved in the pathogenesis of gout, has been extensively investigated, it is still unclear whether soluble UA can trigger a systemic inflammatory response. In gouty arthritis, MSU crystal deposition initiates, amplifies and sustains the local inflammatory processes. There is strong evidence that UA crystals stimulate the release of chemokines and pro-inflammatory cytokines including TNF-a, interleukin-1beta (IL-1b) and IL-6. At present, the evidence in favor of the pro-inflammatory role of soluble UA is limited to few studies performed in vitro and in experimental animals (26-28) and no data is available from human models.

The hypothesis of a pro-inflammatory role of UA contradicts current views on the physiology of UA in humans. As mentioned above, UA is thought to be a powerful antioxidant which is produced physiologically to limit the radical oxygen species (ROS)-mediated cell damage during severe oxidative stress conditions. It has been proven that ROS can trigger an inflammatory response via activation of the Nuclear Factor k-B (NF-kB) pathway. Thus, UA by blocking the effect of ROS should be theoretically considered also an anti-inflammatory factor, and the most important and powerful circulating antioxidant compound.

Understanding the relationship between UA and inflammation is essential to plan effective treatment strategies in clinical practice: if UA levels in the upper portion of the normal range do not contribute to the onset/worsening of inflammation but rather limit the ROS damage in particular pro-inflammatory states, then treatment should be limited to patients who have UA concentrations associated with risk of crystal precipitation. On the contrary, if soluble UA directly stimulates the inflammatory response and this potentially harmful mechanism overcomes the potential benefits related to antioxidant activity, then the treatment should be started early, when UA concentration are still in the upper portion of the normal range.

**UA, Inflammation, and Oxidative Stress: Possible Molecular Pathways**

Multiple and potentially self-maintaining biologic pathways linking UA with inflammation are theoretically possible (Figure 1). Only some pieces of this hypothetical molecular puzzle have been experimentally confirmed and mostly in animal models.

**Figure 1**: The theoretical pathways of the relationship between UA, inflammation and oxidative stress. ROS: Radical Oxygen Species; NFkB: Nuclear Factor-kappa B; XDH: Xanthine Dehydrogenase; XO: Xanthine Oxidase.

Conceptually, three non-mutually exclusive mechanisms can be hypothesized:

A) UA causes inflammation by direct or indirect stimulation of NF-kB (Figure 2).

B) Pro-inflammatory cytokines stimulate the UA production by up-regulating xantine-oxidase (XO), the enzyme that catalyzes the transformation of hypoxantine to UA, leading to increase in UA (Figure 3).

C) A “third factor” stimulates in parallel the synthesis of both pro-inflammatory cytokines and UA. The third factor may increase cell death (apoptosis), or increases ROS production (Figure 4).

**Hypothesis A: UA causes inflammation by directly or indirectly stimulating NF-kB.**

This hypothesis is supported by the results of experiments conducted on mouse smooth muscle cells. The addition of UA in the culture medium activates the intracellular cascade leading to the activation of the NF-kB and AP-1 pathway (via ERK1/2 and p38/MAPK). NF-kB is an essential intracellular factor which regulates, at nuclear level, the transcription of virtually all pro-inflammatory cytokines. The intracellular events triggered by UA determine the production of monocyte chemoattractant protein-1 (MCP-1) and platelet-derived growth factor (PDGF) (29, 30) which are molecules involved in the inflammatory response and in the atherogenetic processes.

Additionally, it has been shown that UA stimulated the production of pro-inflammatory cytokines in mouse mononuclear cell lines. The authors suggested that this effect is mediated by the activation of the NF-kB pathway. However, to the best of our knowledge, this study has only been presented in a scientific meeting and never published in a peer-reviewed journal.

**Hypothesis B: Pro-inflammatory cytokines stimulate the UA production.**

Pro-inflammatory cytokines up-regulate xantine oxidase (XO) activity, which catalyzes the transformation of hypoxantine to UA, leading to increasing UA production. This hypothesis is supported by previous studies showing that the XO gene expression is markedly stimulated by the pro-inflammatory cytokines TNF-α, IL-1β and IFN-γ in bovine renal epithelial cells (31), rat alveolar macrophages (32), and human mammary epithelial cells (33). In addition, a recent study

demonstrated enhanced XO activity in the lungs of rats insufflated with IL-1 and IFN-γ (34). Evidence that TNF-α and IL-1β upregulate the XO gene transcription have been also found by studying airway lining fluid in patients with COPD(35).

**Hypothesis C: A “third factor” stimulates in parallel the UA and cytokines synthesis**. The most likely factor that stimulates the production of both pro-inflammatory cytokines and UA may be an excess of oxidative stress caused by increased ROS production, which can activate the NF-kB pathway (36). The NF-kB activation may increase inflammation, and in turn upregulate xantino-oxidase (see hypothesis B). Moreover, ROS may cause direct and indirect DNA damage (37) increasing the release of damaged purines during the DNA repair. Since purines are the physiologic substrate for XO activity, ROS may up-regulate the XO activity and increase the UA levels, indirectly. Higher XO enzyme activity may in parallel cause higher ROS levels (through a mechanism that involves Vit A) and through this mechanism stimulate the NF-kB pathway bringing about cytokine production in a vicious cycle.

**2. Objectives**

Primary Objective

The primary outcome is to ascertain whether UA is a pro-inflammatory compound. This aim will be tested both by measuring the concentration of inflammatory markers after short term changes in UA, and by testing the hypothesis that different concentrations of UA modify the inflammatory response induced by a lipid tolerance test.

Secondary Objectives

To document the effect of increasing versus decreasing UA levels on circulating antioxidant biomarkers. To test the hypothesis that increasing levels of UA are associated with higher mitochondrial efficiency as indicated by higher MRI-spectroscopy estimated rate of phosphocreatinine resynthesis after exercise.

Both primary and secondary aims will be tested using two different trials whose results will be complementary. In the first trial (Trial A: UA versus Placebo), the primary and secondary outcomes will be estimated after raising the circulating UA levels by systemic UA infusion.

In the second trial (Trial B: Rasburicase versus Placebo), the primary and secondary outcomes will be estimated after lowering the circulating UA levels by systemic infusion of Rasburicase, a recombinant form of urate oxidase that is already approved for clinical use.

In both Trials, measures will be conducted before and after the intervention and the analysis will be focused on a comparison between active treatment and placebo groups.

**Rationale for the double approach**

Using treatments that result in both an increase and a decrease in the circulating UA levels will help to clarify whether UA is a causal, compensatory or co-incidental factor associated with modification of the inflammatory status.

**In Trial A:** UA versus Placebo, UA systemic infusion will rapidly increase the circulating UA levels. We expect that the sudden increase of circulating UA levels may directly affect circulating levels of cytokines and antioxidant biomarkers and affect (increase or reduce) the inflammatory response induced by a lipid tolerance test.

**In Trial B:** Rasburicase versus Placebo, Rasburicase systemic administration will rapidly lower the circulating UA levels. We expect that a sudden decrease of circulating UA levels may affect circulating cytokines and antioxidant biomarkers as well modify the inflammatory response induced by a lipid tolerance test with an opposite fashion compared to Trial A. Both short term approaches of Trial A: UA versus Placebo and Trial B: Rasburicase versus Placebo are likely to allow a better understanding of the possible mechanisms that link changes in circulating UA levels and increased cardiovascular risk. A similar approach has been used by previous studies exploring the effect of sudden changes of saturated fats or circulating homocysteine concentrations, on physiological parameters (39, 40).

**3. Study Design and Methods**

This is a prospective placebo-controlled study, which consists of two inter-related trials, Trial A: UA versus Placebo and Trial B: Rasburicase versus Placebo respectively. Participants will be community-dwelling women and men, aged 50-75 years with BMI 23-34.9 kg/m2. All participants must be capable of attending an outpatient setting at the required protocol time-points.

Participants will be randomized into either Trial A or Trial B: Trial A: UA versus Placebo; and Trial B: Rasburicase versus Placebo. All specific inclusion/exclusion criteria are explained in detail in the remainder of this document.

According to the sequence of enrollment, eligible participants will be randomly assigned to treatment or placebo until 5 pairs of participants (1 intervention and 1 control subject) have been enrolled in each cohort (see the follow Enrollment schema). The randomization list will be maintained by the protocol study monitor. Two sealed copies of the randomization list will be stored at the NIA; one with the PI and one secured in the NIA Research Pharmacy. Study investigators and participants will be blinded to the treatment/placebo assignments. However, NIA research pharmacist or a person designated by him/her will not be blinded, since the medications will be prepared and dispensed to subjects from the NIA Research Pharmacy. The P.I. or designated NIA physician will review the laboratory results with the identity of the subject kept anonymous.

**Trial A: UA versus Placebo**

Twenty participants will be enrolled in this trial, 10 men and 10 women respectively. In each sex group, 5 individuals will be randomly assigned to intervention and 5 to placebo treatment. All participants should have UA ≤10.0 mg/dL and satisfy the inclusion/exclusion criteria reported in section 4C.

**Trial B: Rasburicase versus Placebo**

Twenty participants will be enrolled in this cohort, 10 men and 10 women. In each sex group, 5 individuals will be randomly assigned to intervention and 5 to placebo treatment. All participants should have UA ≤10.0 mg/dL and satisfy the inclusion/exclusion criteria reported in section 4C.

Enrollment schema

**Screening:**

**Uric Acid ≤10.0 mg/dL**

**Trial A**

**Uric Acid**

**≤ 10.0 mg/dL**

**Trial B**

**Men (10)**

**Random Allocation**

**Women (10)**

**Random Allocation**

**Men (10)**

**Random Allocation**

**Women(10)**

**Random Allocation**

**Screening:**

**Age 50**

**-**

**75 yrs**

**BMI 23**

**-**

**34.9 Kg/m2**

**Eligibility: Inclusion/Exclusion criteria are satisfied**

**5 Cases**

**5 Controls**

**5 Cases**

**5 Controls**

**5 Cases**

**5 Controls**

**5 Cases**

**5 Controls**

**Enrollment**

**4. Patient Eligibility and Exclusion Criteria**

*a. General Inclusion criteria valid for both trials*

1. Age 50-75 years
2. BMI 23-34.9 kg/m2
3. Estimated GFR >60 mL/min
4. Blessed mental score equal to or less than 3
5. Ability to fully participate in an informed consent process

6. For Trial A (UA versus Placebo): all participants should have UA ≤10.0 mg/dL

7. For Trial B (Rasburicase versus Placebo): all participants should have UA ≤10.0 mg/dL

*b. General Exclusion criteria for potential participants of both trials*

1. Uric Acid level greater than 10.0 mg/dL.
2. History of hypersensibility or intolerance to Rasburicase and/or to Lithium
3. Chronic Kidney Disease.
4. History of kidney stones.
5. History of asthma, atopic allergies, hemolytic or methemoglobinemia reactions
6. History of unstable angina, cardiac arrhythmia, stroke or myocardial infarction within 3 months, open-heart surgery within 6 months of the study enrollment
7. History of drug or alcohol dependence, or positive urine toxicology
8. Past or present positive test for HBV, HCV or HIV (base on blood test).
9. Glucose-6-Phosphate Dehydrogenase deficiency (G6PD-deficiency)*
10. History of gout
11. Last menstruation occurred less than 1 year ago
12. Unintentional or intentional weight loss of 5 kg in the previous 6 months
13. Alcohol daily intake >30 grams (more than 2 beers daily, more than 2 glass of wine or cocktail daily)
14. Current smokers or former smokers (stopped smoking less than 1 year before)
15. Blood pressure > 150/90 mmHg
16. Diabetes mellitus on dietary or pharmacological treatment
17. Hb <11.5 g/dL in women or < 12.5 g/dL in men
18. Acute infection/inflammation (CRP>5 mcg/mL) for Trial A: UA versus Placebo, CRP >10mcg/L for Trial B: Rasburicase versus Placebo, or any clinical overt chronic infections including periodontal disease.
19. Active liver disease or liver function tests greater than 2 times upper normal limit
20. Self reported inflammatory joints or autoimmune diseases
21. Treatment over the last 3 months with Allopurinol, Rasburicase
22. Treatment over the last 3 months with Warfarin, Dicumarol, Theophylline, Statins
23. Necessity of daily treatment with NSAID
24. Current hormone replacement
25. Ongoing glucocorticoids, corticosteroids, including prednisone and/or cortisone injections or inhalations. (topical steroid cream use and occasional corticosteroid administration over the last 3 months is acceptable)
26. Current daily antioxidants or/and multivitamin supplementation or over the last month
27. Life-threatening diseases including malignancies
28. Recent Blood Donation (last 56 days)
29. Any other reason that based on the PI’s judgment requires exclusion from this study
30. Inability to obtain venous access.

*The Glucose-6-Phosphate Dehydrogenase activity will be assessed in each eligible participant randomly assigned to Trial B. The test for G6PD deficiency will require 3.5 ml of blood.

#Participants will be asked to refrain from taking any NSAIDs during the five days prior before the baseline evaluation and over the course of the study with the exception of Aspirin 100 mg/daily or less.

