**Visit 1: Screening Tests**

Prior to attending the screening visit, each potential participant will be asked to fast overnight (> 8 hours). This screening visit will be conducted under the NIA Uric Acid protocol number 2008-322. After the reviewing the study schema in detail and obtaining protocol, HIPAA, and HIV consents, potential participants will be screened for study eligibility by assessing medical history, physical examination, blood draw (26.5 ml), routine urinalysis, vital signs, height and weight (used to compute BMI) and waist circumference. EKG will be performed at baseline. Cognitive status will be assessed using the Blessed Mental Test and potential participant with a score> 3 will be excluded. Complete CBC with differential count, glucose, BUN, creatinine, UA, LDH, CPK, electrolytes (Na+, K+, Cl-; Ca++, Mg+), AST, ALT, ALP, albumin, globulin, bilirubin (total and direct), haptoglobin, HDL-LDL and Total cholesterol, triglycerides, and CRP will be estimated from blood samples. We will also test for HCV, HBV and HIV. The Glucose-6-Phosphate Dehydrogenase activity will be assessed in each eligible participant randomly assigned to Trial B (individuals who are glucose-6-phosphate dehydrogenase deficient cannot break down hydrogen peroxide, a byproduct of rasburicase, leading to hemolysis). In addition, we will tests potential participants for drug use (urine toxicology test). Urine analysis will be also performed to rule out urinary infections. Finally, urine pregnancy tests will be performed on all women of childbearing age. Since the average age of menopause in the U.S. in 51±4.1 years, all women under age 60 will be considered of childbearing age, with the exception of those who have had their uterus surgically removed. All these tests are aimed at screening for conditions that are considered exclusion criteria for this study, and are performed according to standard clinical methods. A physician will review subject’s medical history, physical exams, EKG and biological tests in order to evaluate the participant’s eligibility criteria. Subjects who are found to be eligible for the study will be scheduled for Visit 2. Those assessed as ineligible will be notified within one week. When notified of eligibility, participants will be instructed on NPO criteria for Visit 2. The participants will receive the following instructions written on an hand-out: 1. To maintain the same dietary habits they had before being involved in the study; 2. In particular not to change their dietary habits by increasing high-purine sea foods, such as anchovies, sardines, herring, mackerel, and scallops, high-purine meats, such as game meats, liver, beef, kidney, brains, meat extracts (e.g. Oxo, Bovril), meat gravys, pork, poultry, and sweetbreads, and high-purine vegetables, such as asparagus, green peas, cauliflower, spinach and mushrooms, lentil, dried peas and beans, and to continue to consume vegetables, oatmeal, wheat bran and wheat germ in the same portions as before. Participants will be advised that changes in their habitual diet may result in a substantial change of their circulating UA levels and that, if so, their participation in the study will be discontinued.

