**Schema of Blood Collection/Analysis**

|  | **Visit 1**  **(T0)** | **Visit 2**  **(T1)** | | | | | | **Visit 3**  **Inpatient (T2)** | | | | | | | | | | | | | **Visit 4**  **(T3)** |
| --- | --- | --- | --- | --- | --- | --- | --- | --- | --- | --- | --- | --- | --- | --- | --- | --- | --- | --- | --- | --- | --- |
|  | Outpatient | Outpatient | | | | | | Day 1 | | | | | | | Day 2 | | | | | | Out |
| **Type of Visit** | Screening | Base | 0 | 2 | 4 | 6 | 8 | Base |  | 1 | 2 | 4 | 8 | 12 | 24 | 0 | 2 | 4 | 6 | 8 | 2 weeks |
| Blood tests1 | **X** |  |  |  |  |  |  |  |  |  |  |  |  | **X** |  |  |  |  |  | **X** |
| Lipid Tolerance Test2 |  | **X** |  | **X** | **X** | **X** | **X** |  |  |  |  |  |  | **X** |  | **X** | **X** | **X** | **X** |  |
| G6PD activity3 | **X** |  |  |  |  |  |  |  |  |  |  |  |  |  |  |  |  |  |  |  |
| UA + Hypoxanthine4 |  |  |  |  |  |  |  | **X** | **X** | **X** | **X** | **X** | **X** | **X** |  |  |  |  |  | **X** |
| PAXgene (RNA)5 |  |  |  |  |  |  |  | **X** |  |  |  |  | **X** | **X** |  |  |  |  |  | **X** |
| DNA Extraction6 |  | **X** |  |  |  |  |  | **X** |  |  |  |  |  |  |  |  |  |  |  |  |
| Inflammatory markers7 |  | **X** |  | **X** | **X** | **X** | **X** | **X** | **X** | **X** | **X** | **X** | **X** | **X** |  | **X** | **X** | **X** | **X** | **X** |
| Antioxidant markers8 |  |  |  |  |  |  |  | **X** | **X** | **X** | **X** | **X** | **X** | **X** |  |  |  |  |  | **X** |
| Ox damage markers9 |  |  |  |  |  |  |  | **X** | **X** | **X** | **X** | **X** | **X** | **X** |  |  |  |  |  | **X** |
| Blood volume draw | 26.5 ml | 45 ml | | | | | | 256.5 ml | | | | | | | | | | | | | 49 ml |

**1.** Complete CBC with differential count, Glucose, BUN, Creatinine, UA, LDK, CPK, Electrolytes (NA+, K+, CL-; CA++, MG+), AST, ALT, ALP, Albumin, Globulins, Bilirubin (total and direct), Haptoglobin, LDL-HDL and total cholesterol, Triglycerides, and CRP.

**2.** Measures obtained at each point: IL-6, IL-6sr, TNF-α, TNF-r1, TNF-r2, sgp 130, and hsCRP +Tryglycerides+1 mL of serum for banking purposes.

**3.** G6PD activity, once in the study.

**4.** UA+Hypoxanthine..

**5.** PAXgene, 5 mL per point. Total volume for 4 points 20 mL.

**6.** DNA extraction, once in the study: Total volume 5 mL.

**7.** Measures obtained at each point: IL-1ra, IL-6, IL-6r, IL-18, IL-1β, TNF-α, TNF-r1, TNF-r2, sgp130 and hsCRP + 1ml of serum for storage.

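### Exclusion 18 gives the Trial B CRP limit in mcg/L, which makes it 500 times stricter than the Trial A limit in the same sentence

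*Protocol*

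**What the plan says.** Section 4b, item 18, excludes people with acute infection or inflammation and defines this by CRP: "CRP>5 mcg/mL) for Trial A: UA versus Placebo, CRP >10mcg/L for Trial B: Rasburicase versus Placebo". No other part of the protocol gives a CRP limit. Section 3 sends the reader to a section 4C for trial-specific criteria, but section 4 as shown has only parts a and b.

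Section 3 also states: "Participants will be randomized into either Trial A or Trial B". CRP is measured at Visit 1 (section 5, Visit 1: Screening Tests), and the outcome of that visit decides who goes on: "Subjects who are found to be eligible for the study will be scheduled for Visit 2".

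On G6PD, the Visit 1 text says: "The Glucose-6-Phosphate Dehydrogenase activity will be assessed in each eligible participant randomly assigned to Trial B". It then says of the Visit 1 tests as a group: "All these tests are aimed at screening for conditions that are considered exclusion criteria for this study". The footnote to section 4b adds: "The test for G6PD deficiency will require 3.5 ml of blood". The blood collection schema marks the sample at Visit 1 with the note "G6PD activity, once in the study". No visit is named for the assignment to Trial A or B. The visit schedule has one randomisation entry, at the Visit 3 baseline, and the Visit 3 text describes that step as allocation to treatment or placebo.

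**The concern.** Two limits for the same analyte, serving the same purpose, stand in one sentence in different units. The larger number belongs to Trial B, which suggests a looser limit was meant. The unit turns it into a far stricter one.

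An eligibility limit has to be applied as written. If staff apply this one literally, they turn away from Trial B people whom Trial A accepts. If they apply the limit they think was meant, every Trial B participant with CRP above 0.01 mcg/mL has been enrolled against the written criterion. Neither outcome is wanted.

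The limit also meets the A/B randomisation. Someone who satisfies only one trial's limit cannot properly be randomised between the two, and the protocol does not say what happens to such a person. Correcting the unit moves this problem to a different CRP range but does not remove it.

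**Working it through.** The protocol derives no figure on this point, so there is nothing of its own to reproduce. The check is unit conversion followed by a comparison of ranges.

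**Inputs (section 4b, item 18):** Trial A excludes above 5 mcg/mL; Trial B excludes above 10 mcg/L.

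**Conversion (1 mcg/mL = 1,000 mcg/L):**
- Trial A: 5 × 1,000 = 5,000 mcg/L.
- Trial B: 10 / 1,000 = 0.01 mcg/mL.
- Ratio: 5,000 / 10 = 500. Trial B is 500 times stricter.
- Example: CRP of 1 mcg/mL is within the Trial A limit and exceeds the Trial B limit by 1 / 0.01 = 100 times.

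**If the unit is a slip (assumption; the protocol does not give the intended unit):**

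| Trial B limit read as | In mcg/L | Relative to Trial A | Relative to the written limit |
|---|---|---|---|
| 10 mcg/L (as written) | 10 | 1/500 | 1 |
| 10 mcg/mL | 10,000 | 2 | 1,000 |
| 10 mg/L | 10,000 | 2 | 1,000 |
| 10 mg/dL | 100,000 | 20 | 10,000 |

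The two likely readings, mcg/mL and mg/L, are the same concentration.

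**Who is eligible for what, on this criterion alone:**

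| CRP (mcg/mL) | As written | If Trial B is 10 mcg/mL |
|---|---|---|
| up to 0.01 | A and B | A and B |
| above 0.01, up to 5 | A only | A and B |
| above 5, up to 10 | neither | B only |
| above 10 | neither | neither |

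Only rows marked A and B can be randomised between the trials. As written, that is CRP up to 0.01 mcg/mL. After correction it is CRP up to 5 mcg/mL, and the range above 5 and up to 10 still has no rule. The protocol gives no CRP distribution for the people to be screened, so the number in each row cannot be estimated.

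**Timing of the A/B step.** The trial-specific CRP limit and the G6PD instruction both refer to a trial assignment that has no named visit. One procedure gives a latest time for it. Section 5 (Infusion of the Study Drug) starts sodium bicarbonate in Trial A on the evening before Day 1 of what it calls Visit 2. That is probably a slip for Visit 3, because only Visit 3 has a Day 1 and contains the infusion. On either reading the assignment must precede the Visit 3 baseline, where the only randomisation entry stands.

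**The case against.** The strongest reply on CRP is that this is a visible typing slip. The criterion is meant to pick out acute infection or inflammation, and a limit 500 times below the companion limit for the same purpose cannot be intended. The first Trial B candidate would bring it to light, and staff would be unlikely to enforce it literally. This limits the practical harm, and the fault is one of wording rather than design. It does not make the criterion correct: nothing else in the protocol supplies the right value, and enrolling on a guess departs from the written text.

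A second objection concerns the intended value. The Precis describes Trial B as recruiting people with moderately elevated uric acid, which might explain a deliberately looser CRP limit. That support is weak now that both trials share one uric acid ceiling; for Trial B, section 4a says: "For Trial B (Rasburicase versus Placebo): all participants should have UA ≤10.0 mg/dL". So 10 mcg/mL remains an assumption for the sponsor to confirm.

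On G6PD, a reader might infer that the test cannot be triggered in time and that a deficient person could be given rasburicase. The protocol does not support this. Deficiency is exclusion 9, testing is required in everyone assigned to Trial B, and physicians review eligibility at Visits 1 and 2. The blood schema marks the tube at Visit 1 without limiting it to Trial B, so it can be drawn then and assayed once the trial is known. The enrolment schema, although broken in the text available, appears to place the A/B split at screening, with arm allocation below it. What stands is only that no visit is named for the A/B step.

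**Conclusion.** The point holds for the CRP limit. Item 18 as written bars from Trial B anyone above 0.01 mcg/mL, a limit 500 times stricter than that of Trial A. The conversion needs no assumption. That 10 mcg/mL was meant, which would be twice the Trial A limit, is an assumption.

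The unit should be corrected because it decides who may enter Trial B, and the correction is simple. It needs to come with a rule for people above 5 and up to 10 mcg/mL, since two unequal limits do not fit a randomisation between the trials.

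A reader might infer that the slip biases the results or undermines the power calculation. The protocol does not support that: within each trial both arms face the same limit, and the sample size in section 11 does not use CRP. The missing visit for the A/B assignment is a matter of detail, not a safety gap.

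**What to change.** 1. **Section 4b, item 18.** Correct the Trial B unit, presumably to >10 mcg/mL (10 mg/L), once the sponsor confirms it, and state both limits in the same unit.
2. **Sections 3 and 4b.** Choose one of two rules:
   - use a single CRP limit for both trials, which is simpler and lets the criterion be applied at Visit 1 without knowing the trial; or
   - keep two limits and state that people with CRP above 5 and up to 10 mcg/mL are eligible for Trial B only and are not part of the A/B randomisation. They would still be randomised to rasburicase or placebo within Trial B.
3. **Minor clarification, section 3 and the visit schedule.** Name the visit for the A/B assignment, after the Visit 1 results and before the first Trial A bicarbonate dose. Require a normal G6PD result on file before any Trial B infusion.

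The cost is one corrected unit, one or two sentences and one schedule row. Sample size, visits and blood volumes do not change. No extra G6PD assays are needed if the Visit 1 tube is assayed only for people assigned to Trial B.
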